**Results:**

Ethics approval has been obtained. In March 2022, database owners were contacted to present the project and discuss the request for data. A unique identifier will be used. In July 2023, a process of redefinition of the variables per database was initiated. Data were received in October and November 2023. In November 2023, further work was conducted. By April 2024, we expect to start analyzing the full data set.

**Conclusions:**

The results will contribute to the accumulating body of knowledge and might have relevance to guide global BCG vaccination policy. Data linkage can contribute to a swifter mechanism to use available health data to conduct population-based studies and inform policy decision-making.

**Trial Registration:**

ClinicalTrials.gov NCT05471167; https://clinicaltrials.gov/study/NCT05471167

**International Registered Report Identifier (IRRID):**

DERR1-10.2196/55332

## Introduction

### Background

Immunization has led to a significant decrease in mortality in children under 5 years of age. Several studies have demonstrated that the reduction in mortality and morbidity due to vaccination extends beyond the targeted infections. This seems to result from broader nonspecific effects (also termed heterologous immunity) stemming from the synergistic effects of several live vaccines [1-4]. The vaccines demonstrated to have nonspecific effects include the Bacillus Calmette-Guérin vaccine (BCG), polio vaccine, and measles vaccine [5]. Overall, the nonspecific effects of vaccines vary according to age, sex, time to administration, last vaccine administration, previous and concurrent infections and immunizations, interval between vaccines, genetic factors, nutritional state, season, and co-administration of other immunomodulating agents [1].

BCG is a live attenuated vaccine against tuberculosis (TB), which is administered to newborns ideally at birth or before the seventh day of life. Despite its low efficacy for preventing primary infection or reactivation of latent pulmonary infection and TB infection, BCG is effective against childhood tuberculous meningitis and miliary disease [6]. Hence, BCG at birth is recommended in settings with a high incidence of TB, and it is parsimoniously administered in countries with a low incidence and has been removed from routine vaccination schemes in high-income countries with a low TB incidence [7].

BCG was introduced in the 1920s in Sweden, where it quickly became apparent that the all-cause mortality was lower in BCG-vaccinated children than in those not vaccinated [8]. In England and the United States, the same pattern was observed between the late 1940s and early 1960s, where a reduction in mortality from diseases other than TB was estimated in 25% of vaccinated children (95% CI 6%-41%) [1,9]. Later studies showed the same pattern in infant mortality and morbidity [10], as well as in morbidity in the neonatal period [11]. Furthermore, BCG is used as a standard treatment for carcinoma of the bladder and influences the natural history of infectious and neoplastic diseases [1]. More recently, the effect of BCG was tested in viremia after SARS-CoV-2 exposure [12].

Further studies in children from Denmark and Greenland failed to show a decrease in hospitalization due to infectious diseases in vaccinated children [13,14]. On the contrary, a cohort study of children from 19 different countries revealed that BCG-vaccinated children under 5 years of age had a lower risk of suspected acute lower respiratory infection [15]. In Spain, hospitalization rates due to respiratory infection were lower in BCG-vaccinated children, with an attributable fraction of 32% for children under 1 year of age, and a similar finding was noted for sepsis, with an attributable fraction of 53% [16].

A systematic review concluded that BCG has a beneficial effect on mortality in children, with differential effects according to age (earlier administration of the vaccine is associated with greater effects) [5]. Nevertheless, there has been a call for more research on the nonspecific effects of BCG [5,17]. Currently, studies are seeking to further investigate the nonspecific effects of BCG [18] in terms of the effects on allergy and infection [7], severe morbidity, nonaccidental hospital admission, and all-cause consultation in children under 5 years of age [19].

### BCG Vaccination in Portugal

In Portugal, BCG began to be routinely administered to all newborn children in 1965. Until 2016, a single BCG dose was administered to all newborns, typically before discharge from the maternity ward (most births in Portugal are hospital-based) or as early as possible thereafter [20].

In June 2016, a clinical guideline established that only children under 6 years of age who belong to high-risk groups (those originating from countries with high TB incidence; having contact with active cases or persons under prophylaxis; having HIV-positive mothers; having parents with a alcohol or drug abuse problem and antecedents of TB; having parents who have been in prison in the last 5 years; living in high-risk TB communities; or traveling to high-incidence countries) should be vaccinated as close to birth as possible [21]. Some of these risks were not considered individually but by proxy, with some parishes (freguesias) thus considered high risk for the criteria defined.

In 2016, 42% of children under 1 year of age had received BCG (compared to 98% in the previous year) [20]. Between 2016 and 2018, the incidence of TB increased by 16% in children under 1 year of age (from 7.0 to 8.1 per 100,000 inhabitants) and 192% in children aged 1 to 5 years (from 2.6 to 7.6 per 100,000 inhabitants) [20].

Between the adoption of the high-risk strategy for BCG vaccination in 2016 and 2018, the infant mortality rate (IMR) remained stable at 3.2‰ to 3.3‰, with important variations between the considered years [20]. In 2019, there was a decrease to 2.8‰. The mortality rate in children under 5 years of age decreased from 3.4‰ in 2016 to 3.0‰ in 2019, but not constantly in this period (eg, during 2018 it was 3.5‰) [20]. No death in children under 5 years of age has been attributable to TB since the implementation of the high-risk strategy for BCG [20]. Nevertheless, the number of severe cases of TB in children under 5 years of age decreased in 2020 compared to 2018 (4 cases) and 2019 (7 cases), with just 1 case registered in a child without BCG vaccination [22].

### Evaluation of the BCG Vaccination Policy

Since the implementation of the high-risk strategy for BCG in 2016, no assessment has been conducted regarding the impact of the BCG policy shift on severe, moderate, or mild morbidity and on mortality in children. It is a common problem that vaccination practices are changed without evaluating the overall health effects of the change and that the nonspecific effects of vaccines are not included in the considerations regarding vaccine policies.

In 2021, the first cohort of children not vaccinated for BCG completed the fifth year of life, and evidence is needed regarding the impact of this strategy, especially given fluctuations in the IMR, a decline in the TB notification rate not accompanied by a decline in the incidence, a higher TB incidence in greater metropolitan areas, and a high median number of days from symptoms to diagnosis [22].

No data have been gathered on overall hospital admissions and morbidity patterns. Similarly, no data have been compiled on the BCG strains used in the country and their differences in terms of efficacy. This evidence will have a bearing on the continuity of the current strategy.

The need for more and better evidence is paramount, especially given that besides deciding on the inclusion of BCG in the country’s immunization plan, arguments on the nonspecific effects of vaccines (and not only of BCG) can help overcome vaccine hesitancy. In high-income countries, including Portugal, vaccine hesitancy has been responsible for a decline in coverage rates and for the re-emergence of severe cases of vaccine-preventable diseases such as measles [23,24].

### Hypothesis

Given the described effects of BCG on overall mortality, immune and atopic conditions including asthma, and incidence of respiratory tract infections; its nonspecific protection against nonrelated pathogens; and its protective effects that are apparent shortly after immunization and sustained for at least 1 year [2,25], we hypothesize that some of the variations in mortality among children under 5 years of age, in the incidence of TB, and in severe, moderate, and mild morbidity among children under 5 years of age might be partially explained by a reduction in the coverage rate of BCG since 2016. The reduction in the coverage rate of BCG, which resulted from only high-risk children receiving BCG at birth, might have prevented nonvaccinated children from developing trained immunological responses as effectively as BCG-vaccinated children.

### Objectives

We aim to investigate the incidence of the specific and nonspecific effects of BCG by comparing the incidences of TB disease and infection; mild, moderate, and severe morbidity; and mortality in the first 5 years of life among children born in Portugal between 2010 and 2021, according to their BCG status.

## Methods

### Study Design

This population-based historical (retrospective) birth cohort study will compare the incidence of all-cause mortality (including due to TB disease); TB disease; and severe, moderate, and mild morbidity between BCG-vaccinated and nonvaccinated children born between July 1, 2010, and June 30, 2021.

### Setting

This study will investigate the specific and nonspecific effects of BCG based on the shift in the BCG vaccination policy that occurred in Portugal in July 2016, when a consistently low incidence of TB led to the revision of the National Immunization Plan. Since then, BCG has been administered only to newborns considered to be at higher risk of TB infection, thus creating an opportunity to compare BCG-vaccinated and nonvaccinated children.

The approach adopted by Portuguese public health authorities to define the high risk for TB was based on geographical risk, with, for instance, all children born in some parishes in the metropolitan areas of Lisbon and Porto being offered BCG independent of socioeconomic status, country of origin, or vulnerability. We believe that this type of risk definition has guaranteed enough variability between BCG-vaccinated and nonvaccinated children, thus allowing comparisons of health outcomes between exposed and nonexposed children.

### Participants

The study will include children under 5 years of age born and registered in Portugal between July 1, 2010, and June 30, 2021. We have chosen this period because it will allow us to (1) compare the cohorts before and after the change in the BCG immunization strategy (Figure 1); (2) characterize children not vaccinated with BCG and their health outcomes (when universal BCG at birth was recommended); and (3) compare children exposed and not exposed to BCG after the 2016 change in the BCG vaccination strategy.

**Figure 1 figure1:**
[figure not shown]
Lexis graph. BCG: Bacillus Calmette-Guérin vaccine.

#### Eligibility Criteria

The study will include children born alive in Portugal (births coded as diagnosis-related group [DRG] 795 [normal newborn]).

#### Exclusion Criteria

The study will exclude newborns who have a weight of <2 kg, are premature (<37 weeks of gestation), or are known or suspected to have HIV infection.

The follow-up period will be until the completion of 5 years of age or the end of follow-up (June 30, 2021) (Figure 2).

**Figure 2 figure2:**
[figure not shown]
Flowchart. DRG: diagnosis-related group; NHS: National Health Service.

### Data Sources

The study will be based solely on secondary data. The data sources are the National Health Service (NHS) user registry (RNU), Death Certificate Information System (SICO), vaccination registry, communicable diseases surveillance system (Sistema Nacional de Vigilancia Epidemiologica [SINAVE]), surveillance information system for TB (Svig-TB), DRG information system for hospital admissions and visits to the emergency department (Base de Dados de Morbilidade Hospitalar [BDMH]), and primary health care (PHC) information system (SClínico) of children born between July 1, 2010, and June 30, 2021.

The birth registry database (RNU) contains data on gender, age, PHC center where the child is to be followed up, nationality, and place of residence. The SICO database provides data on the cause and date of death. The vaccination registry includes data on the vaccines administered, date of vaccination, and place of residence. The BDMH database gathers data on hospital admissions and emergency department visits to NHS hospitals, including the date of admission and discharge, diagnosis, type of admission, motive for admission, weight at birth, DRG code, major diagnostic category (MDC) code, complications of pregnancy and delivery, and type and place of delivery. Data from admissions at private hospitals are not included. The SClínico database contains data on socioeconomic status and visits (including motive and diagnosis) to NHS PHC units. Svig-TB is a database for notification and follow-up of TB cases, and SINAVE is the general surveillance information system for communicable diseases, including TB, and regarding TB, it contains data on symptoms at presentation, date of diagnosis, type of treatment, other diseases before TB, risk groups, and outcomes of the infection.

### Measurements

Exposure is defined as having received the BCG vaccine during the first year of life and is measured using the vaccination registry. Variables include BCG (yes or no, and number of doses) and time from birth to BCG (in days).

#### Secondary Outcomes

The secondary outcomes include the mortality and morbidity profiles of children under 5 years of age between 2010 and 2021, including causes of death and morbidity, the profiles of nonvaccinated children, and the NHS hospital and PHC utilization profiles of children under 5 years of age before and after 2016 (Table 1).

### Statistical Methods

Through data linkage, we will create a single database that links data from the birth registry, SICO, vaccination registry, SINAVE, Svig-TB, BDMH, and PHC database (SClínico) to reconstruct chronological sequences of morbidity and mortality events from birth until the completion of 5 years of life or the end of follow-up (for the 2018 cohort onwards).

In each of the databases, we will identify the data needed and whether a unique identifier (UI) exists and can be provided with the data set. After having access to the requested data and in case a UI is provided (and common to all databases), we will combine information based on that UI.

In case a UI is not provided, we will link data from several data sets using a range of proxy identifiers (eg, date and place of birth, sex, and place of residence) to identify probable matches.

The type of data linkage method to be used will depend on the type and quality of the linkage variables available in the data sets. However, we anticipate having to use a combination of deterministic and probabilistic methods. Before applying linkage methods, we will clean and standardize the data, thus identifying and removing errors and inconsistencies. Given the expected size of the data sets, we will then select sets of block attributes (eg, sex, date of birth, and initials) and compare record pairs with the same matched attributes within blocks. Subsequently, record pairs will be compared for each linkage variable, and an agreement score will be computed. This score will be used to weigh the probability of a record pair belonging to the same child [26,27].

After obtaining the final database, we will compute person-time incidence rates for primary outcomes in BCG-vaccinated and nonvaccinated children. Using the Kaplan-Meier method, we will compute and compare the probability of surviving the first and fifth years of life or of not having a hospitalization, emergency department visit, or mild morbidity episode during the follow-up period according to exposure. Additionally, we will use a log-rank test for assessing differences in survival rates between exposed and nonexposed children and hazard ratios (and corresponding CIs) for quantifying the differences. To explore the effects of several variables on the survival outcomes, we will use proportional hazards regression analysis. If missing data are below 5%, we will use complete case analysis. Otherwise, the frequency and patterns of missing data will be analyzed, and if appropriate, we will use multiple imputation techniques.

Confounders to be measured and controlled for are sex, health unit, completeness and timeliness of vaccination status and scheme, socioeconomic status, and BCG strain (over the years, administered BCG has been provided by different producers, with different strains).

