**Methods:**

This population-based historical birth cohort study includes children under 5 years of age born in Portugal between July 1, 2010, and June 30, 2021. Newborns with low birth weight, premature status, or known or suspected HIV infection are excluded. The follow-up period is until the completion of 5 years of age or the end of follow-up (June 30, 2021). The study will use secondary data from the National Health Service user registry, death certificate database, vaccination registry, communicable diseases surveillance system, TB surveillance system, diagnosis-related group information system for hospital admissions and emergency department visits, and primary health care information system. The data will be linked. Primary outcomes include person-time incidence rates of death (all causes and TB), TB diagnosis, and all causes and some specific causes of severe, moderate, or mild morbidity, and the incidence rate ratio of nonvaccinated to BCG-vaccinated children. We will compare the probability of surviving the first and fifth years of life or of not having severe, moderate, or mild morbidity during the follow-up period according to exposure (BCG vaccinated or nonvaccinated, number of doses, and time from birth until the first dose), using the log-rank test for assessing differences in survival rates between exposed and nonexposed children and hazard ratios for quantifying the differences. Moreover, we will perform a proportional hazards regression analysis.

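### The adjustment set omits birth weight and pregnancy or delivery complications, so residual confounding by newborn condition is possible within the restricted cohort, mainly for BCG timing and the few nonvaccinated children born 2010-2015

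*Protocol article*

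**What the plan says.** The Statistical Methods section gives the adjustment set as a finished list: "Confounders to be measured and controlled for are sex, health unit, completeness and timeliness of vaccination status and scheme, socioeconomic status, and BCG strain". It carries no wording that marks the items as examples.

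Under Data Sources, the hospital database is said to gather, among other fields, "weight at birth, DRG code, major diagnostic category (MDC) code, complications of pregnancy and delivery, and type and place of delivery".

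Newborn condition enters the design through restriction. Eligibility Criteria admits live births ("births coded as diagnosis-related group [DRG] 795 [normal newborn"), and Exclusion Criteria removes "newborns who have a weight of <2 kg, are premature (<37 weeks of gestation), or are known or suspected to have HIV infection".

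Timing is one of the exposures. Measurements states: "Variables include BCG (yes or no, and number of doses) and time from birth to BCG (in days". The abstract's Methods paragraph says survival and freedom from morbidity will be compared "according to exposure (BCG vaccinated or nonvaccinated, number of doses, and time from birth until the first dose".

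On practice before the policy change, the background section on BCG in Portugal says the dose was given "typically before discharge from the maternity ward (most births in Portugal are hospital-based) or as early as possible thereafter". A footnote to Table 1 puts coverage for 2010-2015 at 98.2% to 98.4%.

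**The concern.** If the usual dose is given before the child leaves the maternity ward, a late or missed dose may in part reflect how the child was doing at birth. The same condition plausibly predicts later admission, emergency visits and death. Birth weight and perinatal complications precede the exposure, so they are natural candidates for adjustment. Leaving them out lets part of any difference between early and late vaccination, or between vaccinated and nonvaccinated, reflect who the children were.

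Two comparisons are most exposed:

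- **Time to first dose.** The introduction cites a review in which earlier BCG goes with larger effects. Uncontrolled newborn condition could produce a similar gradient without any effect of timing.
- **Nonvaccinated children born 2010-2015.** When nearly everyone is vaccinated, the small remainder may be strongly selected.

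With around 970,000 children expected, intervals for common morbidity outcomes will be narrow and will not reflect a bias of this kind. The authors see the results as relevant to vaccination policy, so a modest bias would matter.

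**Working it through.** The article states no effect size, power or bias figure on this point, so there is nothing to reproduce. The check has three parts.

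**1. Size of the pre-2016 nonvaccinated group.** Inputs: about 970,000 children (Results), 11 birth years (July 2010 to June 2021), coverage 98.2-98.4% (Table 1 footnote). Assumptions: births spread evenly, national coverage applies to the cohort, and the period July 2010 to December 2015 is 5.5 years.

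- Children born in the period: 970,000 / 11 × 5.5 = 485,000.
- Nonvaccinated: 485,000 × 1.6% = 7,760 up to 485,000 × 1.8% = 8,730.

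This group is large enough to analyse and small enough to be selected.

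**2. Possible size of the bias.** Take one binary marker of poorer newborn condition that survives the restriction, and assume BCG has no effect. The spurious rate ratio for late or no BCG against early BCG is

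[1 + p1(R − 1)] / [1 + p0(R − 1)],

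where p0 and p1 are the marker's prevalence in the early group and in the late or nonvaccinated group, and R is its rate ratio for the outcome. The article gives none of the three, so all are assumed.

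| p0 | p1 | R = 1.5 | R = 2 | R = 3 |
|---|---|---|---|---|
| 1% | 2% | 1.005 | 1.010 | 1.020 |
| 5% | 10% | 1.024 | 1.048 | 1.091 |
| 5% | 20% | 1.073 | 1.143 | 1.273 |
| 5% | 30% | 1.122 | 1.238 | 1.455 |

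For example, p0 = 5%, p1 = 20%, R = 2 gives 1.20 / 1.05 = 1.143. If the vaccinated were instead the frailer group (6% against 2% in the nonvaccinated, R = 4), the ratio would be 1.06 / 1.18 = 0.90.

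**3. Direction for mortality.** Exposure means BCG at any time in the first year, so a child vaccinated late has to be alive at the dose. If person-time runs from birth, deaths that would have occurred before the dose cannot appear in the late group. If those are a share f of its deaths, the null ratio becomes about 1 − f. With f = 25% (assumed) it is 0.75. Combined with a confounding factor of 1.143, the net is 0.75 × 1.143 = 0.86, so late BCG would look protective. With f = 10% the net is 0.90 × 1.143 = 1.03. The two biases pull in opposite directions, and the article does not show which is larger.

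**The case against.** The strongest reply is that the design already handles newborn condition by restriction. Coding as a normal newborn, term birth and a weight of at least 2 kg remove most of the sick and very small babies on whom the argument depends. This largely stands. A reader might infer from the adjustment list that newborn condition goes uncontrolled, and the eligibility criteria do not support that. Restriction does not, however, balance birth weight above 2 kg, or complications compatible with a normal-newborn code.

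Second, after 2016 BCG status followed mainly area-based TB risk. The Setting section says that in some parishes every child was offered BCG irrespective of social circumstances, and health unit and socioeconomic status are adjusted for. This weakens the point for post-2016 status. It does not remove it, because the background section also lists individual criteria and says only some were applied by parish.

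Third, every between-group contrast in Table 1 is by exposure status or birth cohort, and none is by time to dose. That is correct, but the abstract names timing as an exposure for the survival and morbidity comparisons.

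Fourth, the variables may not be available. The Results section says some requested variables were withheld or replaced, and the detail is in an appendix not shown here. No link between mother and child records is described, so pregnancy data may not attach to the child. This stands for complications. Birth weight is different: the 2 kg exclusion cannot be applied without it, and BDMH is the only listed source that is said to hold it.

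Finally, the article is condensed, and model details such as the functional form belong in an analysis plan. The list of confounders, however, is stated here.

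**Conclusion.** The point holds in limited form. The stated adjustment set has no measure of newborn condition although the article describes such fields as held, so residual confounding within the restricted cohort is possible. It matters most for the time-to-first-dose comparison and for contrasts that use the 1.6-1.8% nonvaccinated children born 2010-2015.

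The size is uncertain and may be small: 1.005 to 1.02 if the restriction leaves little residual frailty, and up to about 1.46 under the most unfavourable inputs tried. Every prevalence and rate ratio behind those figures is an assumption.

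A reader might go further and conclude that the plan will make delayed BCG look harmful. The article does not support that. For mortality, survival to the dose acts the other way and may outweigh the confounding. For other outcomes, the association between newborn condition and timing is plausible but not documented.

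**What to change.** In Statistical Methods, add birth weight as a continuous covariate to the proportional hazards models and any adjusted rate models, for both the vaccinated-versus-nonvaccinated and the timing comparisons. Add pregnancy and delivery complications where they were supplied and can be linked to the child. Handle missing values under the plan's existing rule (complete cases below 5% missing, otherwise multiple imputation if appropriate). These variables precede BCG, so adjusting for them does not remove part of a BCG effect.

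If a variable was not supplied, say so, and state residual confounding by newborn condition as a limitation of the timing analysis.

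The cost is about one sentence of text and a few model terms. The downside is missing values for children without a linked NHS birth record.
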